### Intervention

The surgical procedures of the uncut Roux-en-Y arm and Billroth II arm are as follows.

#### Uncut Roux-en-Y arm

After distal gastrectomy, duodenal stump closure, side-to-side anastomosis is performed on the remnant stomach and jejunum, 25 cm from the ligament of Treitz. Then, side-to-side anastomosis between the jejunum approximately 35 cm from gastrojejunostomy and the jejunum approximately 5 cm from the ligament of Treitz is performed. The intestinal cavity on the input less than 5 cm from the loop gastrojejunostomy anastomosis is closed using uncut closure devices.

#### Billroth II arm

After distal gastrectomy and duodenal stump closure, the investigators first perform remnant stomach and upper jejunum side anastomosis. Then, they choose the jejunum approximately 25 cm from the ligament of Treitz, to the premenstrual colon using a disposable cutting closure (or tubular stapling) in the rear wall of the stomach and jejunum anastomosis; common opening is closed with (barbed wire) hand-stitching. Subsequently, the steps are the same as group A (uncut Roux-en-Y arm).

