### Uniformity in surgical performance

Assuring uniformity in surgical performance is the key point for our multi-center clinical trial. Therefore, the surgeons definitely should be trained and the operative procedures monitored. It is worth mentioning that the surgeons should at least have clinical experience in conducting radical gastrectomy for more than 3 years or more than 100 cases.

Before the trial, the leading center will appoint qualified surgeons to train the other surgeons in the coordinating centers. It is relatively easy for them to master the new technique for the reason that the uncut Roux-en-Y anastomosis is based on Billroth II anastomosis with the addition of the side-to-side anastomosis between the jejunum approximately 35 cm from gastrojejunostomy and the jejunum approximately 5 cm from the ligament of Treitz and closure of the intestinal cavity on the input less than 5 cm from the loop gastrojejunostomy anastomosis using uncut closure devices.

In particular, it is required to take pictures of the surgery field including the lymph node dissection area and the anastomosis field in order to make sure that the performance is qualified. These pictures will be uploaded to the database and checked by the data managers. If the operation does not achieve the standard of either D2 gastrectomy or corresponding anastomosis, the case will be rejected.

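### The last sentence of the Billroth II description, as written, gives the control arm the two steps that define uncut Roux-en-Y; probably a drafting slip, but it should be corrected

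*Protocol article*

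**What the plan says.** The protocol article describes the two reconstructions under Intervention.

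- **Uncut Roux-en-Y arm.** After gastrectomy and duodenal stump closure, "side-to-side anastomosis is performed on the remnant stomach and jejunum, 25 cm from the ligament of Treitz". The next step is a "side-to-side anastomosis between the jejunum approximately 35 cm from gastrojejunostomy" and the jejunum about 5 cm from the ligament of Treitz. The last step is the luminal closure: "The intestinal cavity on the input less than 5 cm from the loop gastrojejunostomy anastomosis is closed using uncut closure devices". The description ends there.
- **Billroth II arm.** After gastrectomy and stump closure, the surgeons join the gastric remnant to the upper jejunum; "they choose the jejunum approximately 25 cm from the ligament of Treitz", and the common opening is closed by hand. The final sentence is "Subsequently, the steps are the same as group A (uncut Roux-en-Y arm".

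The section Uniformity in surgical performance explains how the operations relate: "the uncut Roux-en-Y anastomosis is based on Billroth II anastomosis with the addition of the side-to-side anastomosis" and "closure of the intestinal cavity on the input less than 5 cm from the loop gastrojejunostomy anastomosis using uncut closure devices". It also says that a case is rejected if the operation falls short of the D2 standard or of the anastomosis assigned.

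**The concern.** The final sentence of the Billroth II description sends the control arm to whatever group A does after the gastrojejunostomy. The only things group A is described as doing after that point are the jejunojejunostomy and the uncut luminal closure. The uniformity section treats exactly those two steps as the difference between the operations. The two parts of the article cannot both be right.

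The reconstruction is the randomised intervention: the allocation is revealed after the D2 gastrectomy and the assigned anastomosis is then performed (Randomization). The Background credits uncut Roux-en-Y with an anti-reflux function, and the sample size is built on reflux gastritis. The faulty sentence therefore sits in the definition of the comparator and concerns the feature under test. Followed exactly, it would remove the contrast. Followed in part, it would add a jejunojejunostomy to the controls. A reader who wants to apply or repeat the trial also needs a correct description of the control operation.

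**Working it through.** The article gives no figure to reproduce here. The check sets the described steps side by side.

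**Inputs.** The step lists under Uncut Roux-en-Y arm and Billroth II arm, and the statement of the difference under Uniformity in surgical performance.

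| Step after distal gastrectomy | Uncut Roux-en-Y arm | Billroth II arm, without its last sentence | Billroth II arm, last sentence read literally | Named under Uniformity as an addition to Billroth II |
|---|---|---|---|---|
| Duodenal stump closure | yes | yes | yes | no |
| Gastrojejunostomy about 25 cm from the ligament of Treitz | yes | yes | yes | no |
| Side-to-side jejunojejunostomy | yes | no | yes | yes |
| Uncut luminal closure | yes | no | yes | yes |

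1. Without the last sentence, group A has 4 described steps and the control arm 2. Distinguishing steps: 4 − 2 = 2. They are the two that the uniformity section names.
2. With the last sentence read literally, the control arm has 2 + 2 = 4 steps. Distinguishing steps: 4 − 4 = 0.
3. Could the sentence refer to something harmless, such as routine closing steps? The group A description contains none, and nothing in the control description limits the sentence in that way. This reading has to be supplied from outside the text.
4. Could it mean partial sharing, with a jejunojejunostomy but no luminal closure in controls? The sentence does not say so, and the uniformity section rules it out, because it lists the jejunojejunostomy among the additions.

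The count only summarises the literal reading; it does not measure an effect. It treats the control description, which mentions the stomach-to-jejunum anastomosis first in general terms and then with its site and technique, as one gastrojejunostomy. That is the natural reading, but the wording is rough.

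**The case against.** The strongest reply is that no competent surgeon would be misled. The uniformity section states the difference between the operations plainly, the arms carry different names, and the Fig. 1 caption presents two distinct reconstructions. The Background lists Billroth II among the most used techniques. Surgeons need more than 3 years or 100 cases of radical gastrectomy, and before the trial "the leading center will appoint qualified surgeons to train the other surgeons in the coordinating centers". The rough wording of the control paragraph suggests translation or condensation from a fuller operative text, in which the sentence may have pointed to later shared steps. A journal article would commonly leave such steps out.

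Most of this stands. It is good reason to call the sentence a slip and to believe that the intended contrast is recoverable. It does not make the sentence correct. This is not detail left to another document: the article makes a positive statement about the control operation, and its own later section contradicts it. That the sentence may once have referred to unlisted steps is conjecture.

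It can also be said that a correction comes late, since recruitment began on 1 January 2016 and was due to end by December 2018. That limits its value for operations already done. It does not limit its value for the record, for later readers, or for judging whether an operation met its assigned standard.

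**Conclusion.** The point holds as a textual error in the definition of the comparator. As written, the last sentence of the Billroth II description assigns to controls both of the steps that distinguish uncut Roux-en-Y. Confidence in the mismatch is high; that it is a drafting slip is a probable inference, resting mainly on the uniformity section. It should be fixed because it concerns the randomised contrast and the correction costs almost nothing.

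A reader might infer more, and the documents do not support it:

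- **That controls received the experimental operation, or a jejunojejunostomy.** Nothing in the article reports how any patient was operated on, and the training and the uniformity section point the other way.
- **That the contrast is diluted and power lost.** The document gives no input for such a calculation. The planned 12% versus 8%, and the 416 per group, are not affected by this point.
- **That ordinary Billroth II cases would be rejected at the photograph check.** The article does not say that the step lists under Intervention are the standard the data managers apply. Applied literally, the sentence would reject every ordinary Billroth II, so such use is implausible.
- **That the compliance count in the interim report would catch the problem.** The article does not say that compliance there means surgical conformity.

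**What to change.** Delete the last sentence of the Billroth II description. Alternatively, replace it with: *No jejunojejunostomy and no uncut luminal closure is performed in the Billroth II arm.* The replacement should not refer to shared closing steps unless those steps are listed.

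If the investigators do intend a jejunojejunostomy in the control arm, they should say so there and correct the uniformity section, which now counts it as an addition to Billroth II.

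Circulate the corrected step list to the participating centers, so that the anastomosis assigned to each arm has one meaning when an operation is judged against its standard.

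The cost is one sentence and one notice to the centers. Sample size, visit schedule and analysis do not change.

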### Uniformity in surgical performance

Assuring uniformity in surgical performance is the key point for our multi-center clinical trial. Therefore, the surgeons definitely should be trained and the operative procedures monitored. It is worth mentioning that the surgeons should at least have clinical experience in conducting radical gastrectomy for more than 3 years or more than 100 cases.

Before the trial, the leading center will appoint qualified surgeons to train the other surgeons in the coordinating centers. It is relatively easy for them to master the new technique for the reason that the uncut Roux-en-Y anastomosis is based on Billroth II anastomosis with the addition of the side-to-side anastomosis between the jejunum approximately 35 cm from gastrojejunostomy and the jejunum approximately 5 cm from the ligament of Treitz and closure of the intestinal cavity on the input less than 5 cm from the loop gastrojejunostomy anastomosis using uncut closure devices.

In particular, it is required to take pictures of the surgery field including the lymph node dissection area and the anastomosis field in order to make sure that the performance is qualified. These pictures will be uploaded to the database and checked by the data managers. If the operation does not achieve the standard of either D2 gastrectomy or corresponding anastomosis, the case will be rejected.

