### Sample size

Our study is designed as a superiority trial whose primary outcome is postoperative reflux gastritis or not. Current experience suggests the predicted rate of postoperative reflux gastritis will be 8% for the uncut Roux-en-Y anastomosis group and 12% for the control group of Billroth II anastomosis. The difference test was used to estimate the sample size with 80% test power and a 5% significance level. Accounting for a 15% drop-out rate and the 1:1 allocation ratio, the total number of patients required per group is 416 (832 in total), which was calculated using the software PASS version 11.0. Considering a completion rate of 75% for each coordinating center, 1040 envelopes were designed for random allocation. The number of cases will be increased if necessary according to the results of the interim analysis.

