### Randomization

After completing an initial assessment and signing an informed consent form, participants will be randomized into two groups: the experimental group undergoing uncut Roux-en-Y anastomosis and the control group undergoing Billroth II anastomosis.

The randomization is undertaken only by the qualified researchers. A secure randomization routine will give each patient an identification number. This number must be recorded in the randomized list together with the randomized data. The completed list should be signed by the investigators and submitted to the data center along with the patients’ initial information. Patients’ identification numbers should be marked in all the relevant reports.

During the randomization, allocation concealment should be maintained. All the patients will be randomized into groups in a 1:1 ratio, and neither surgeons nor patients will be informed as to the randomization arm before surgery. Once D2 gastrectomy has been performed, the randomization arm of the patient will be revealed and the corresponding anastomosis will be performed.

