Moreover, we plan to do some subgroup analysis using the different preoperative nutrition status or the postoperative pathological stages as analysis factors. In our trial, region supervisors will monitor the researchers with regard to completeness of data collection. However, it is unavoidable to have some missing data. As we mentioned in the “Elimination criteria” section, patients whose efficacy evaluation data for the treatment are incomplete will be excluded. Other missing data are divided into two kinds—important data and common data—depending on the relationship of the missing data and the primary or secondary assessment of the trial. We will record and report the number of cases where the randomized treatment cannot be performed. We will try to fix the common data using statistical tools. However, if the missing data are important, we will employ a specialist of statistics to analyze and decide how to deal with them.

However, bias exists in all clinical trials. In our trial, the blinding of the surgeons and patients as to the intervention is the most challenging aspect of designing a randomized controlled trial involving surgical procedures. For others, the blinding of patients should also be considered to reduce potential bias. Therefore, we set purely objective variables as the primary endpoints, including endoscopy and laboratory tests. Additionally, multicenter trials are associated with biases, including differences in operative skill. We have tried to eliminate these biases by examining the surgical procedure by another hospital and training all surgeons at participating centers in standard procedures.

To conclude, based on previous efforts in the reconstruction of distal gastrectomy, the proposed CSGC002 trial represents a multi-center, prospective, randomized controlled trial to test the hypothesis that uncut Roux-en-Y anastomosis can reduce postoperative complications and improve the nutritional status of gastric cancer patients after D2 gastrectomy compared to Billroth II anastomosis. We believe that the results of the trial will significantly contribute to the evidence on which to base the reconstruction of distal gastrectomy.

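### Cases are rejected on a photo check of the assigned anastomosis, made after randomisation and after the arm is revealed, and nothing keeps them in an as-randomised analysis

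*Protocol article*

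**What the plan says.** The Randomization section sets the order of events: "Once D2 gastrectomy has been performed, the randomization arm of the patient will be revealed and the corresponding anastomosis will be performed". Uniformity in surgical performance then requires photographs of the dissection area and of the anastomosis field. On these it says "These pictures will be uploaded to the database and checked by the data managers", and then "If the operation does not achieve the standard of either D2 gastrectomy or corresponding anastomosis, the case will be rejected". No masking of the check is described.

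The same section compares the two operations: "the uncut Roux-en-Y anastomosis is based on Billroth II anastomosis with the addition of the side-to-side anastomosis between the jejunum", together with closure of the input loop by an uncut device. Of the surgeons at the coordinating centers it says "It is relatively easy for them to master the new technique".

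On cases that do not go to plan, the Discussion says "We will record and report the number of cases where the randomized treatment cannot be performed". Elimination criteria removes patients with too many missed assessments or with efficacy not evaluated as planned, and does not mention surgical quality. Outcome measures says that all enrolled patients are followed, but restricts the final analysis to patients without recurrence. None of these sections says that a rejected case is analysed in its assigned arm.

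On the endpoint, Sample size says "Our study is designed as a superiority trial whose primary outcome is postoperative reflux gastritis or not".

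**The concern.** A patient whose anastomosis is judged below standard has already been randomised and has already received the assigned reconstruction. Dropping that patient selects on the delivery of the treatment, and the standard applied is specific to the arm. Randomisation no longer guarantees that the patients who remain are comparable.

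The two arms are also unequally exposed to the check. The uncut arm contains the Billroth II steps plus two more, in a procedure the surgeons have just been taught, so it has more points at which it can fail. The Background credits this reconstruction with an anti-reflux function. A construction that fails may plausibly carry a higher reflux risk, and removing it would lower the observed reflux rate in that arm.

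The question answered also changes. The trial aims to guide the choice of reconstruction, and technical failure is one of the consequences of that choice. An analysis of accepted cases describes well-performed operations only. The same selection could affect anastomotic ulcer and the perioperative fistula and stenosis listed under Outcome measures.

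**Working it through.** **Is it an exclusion after reveal?** The order in the article is: consent, randomisation, D2 gastrectomy, arm revealed, anastomosis, photographs uploaded, data-manager check, rejection. The anastomosis part of the rule therefore comes after both randomisation and reveal. The D2 part concerns work done before reveal and is less dependent on the arm, although its photo review also follows randomisation.

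**Inputs from Sample size.** Predicted reflux gastritis is 8% (uncut) and 12% (Billroth II), with 416 per group and 15% drop-out. This leaves 416 × 0.85 = 353.6 evaluable per group. The figure of 416 is used here as stated. It could not be reproduced from 12% against 8% at 80% power: a two-sided 5% test needs 882 per group, and 882 / 0.85 gives 1038 after drop-out. That is a separate matter and does not affect this point.

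**Assumed inputs.** The article gives no rejection rate and no outcome for rejected cases. Let f and g be the shares rejected in the uncut and control arms, and q the reflux risk among rejected cases. The true rate is set at 12% in both arms, so that any difference is an artefact.

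**Formulas.**
- Observed uncut rate: pE = (0.12 − f·q) / (1 − f).
- Observed control rate: pC = (0.12 − g·q) / (1 − g).
- Numbers: nE = 353.6(1 − f), nC = 353.6(1 − g).
- Chance of false superiority: Φ[(pC − pE − 1.96·SE0) / SE1], where SE0 is the pooled and SE1 the unpooled standard error. The nominal value is 2.5%, the favourable tail of a two-sided 5% test. The article does not state sidedness, so this is an assumption.

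**Worked case, f = 5%, g = 0, q = 50%.**
- pE = (0.12 − 0.025) / 0.95 = 0.100 and pC = 0.120.
- nE = 335.9 and nC = 353.6.
- Pooled rate = (33.59 + 42.43) / 689.5 = 0.1103.
- SE0 = 0.02386 and SE1 = 0.02380.
- (0.020 − 1.96 × 0.02386) / 0.02380 = −1.12, and Φ(−1.12) ≈ 0.13.

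**Results.**

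| f (uncut) | g (control) | q | Uncut vs control | False superiority |
|---|---|---|---|---|
| 5% | 0 | 12% | 12.0% vs 12.0% | 2.5% |
| 5% | 0 | 30% | 11.1% vs 12.0% | 5.8% |
| 5% | 0 | 50% | 10.0% vs 12.0% | 13.0% |
| 10% | 0 | 30% | 10.0% vs 12.0% | 12.7% |
| 10% | 5% | 30% | 10.0% vs 11.1% | 6.4% |
| 10% | 10% | 30% | 10.0% vs 10.0% | 2.5% |

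A gap of 2 points is half the planned difference of 12 − 8 = 4 points. The formulas are symmetric: if the control arm lost more cases at the same risk, the artefact would run against uncut Roux-en-Y. If rejected cases are kept in their assigned arm, this rule contributes no bias.

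**The case against.** The rule is written for both arms and also covers D2 quality. The article does not say what a case is rejected from: the trial, follow-up or one analysis set. Outcome measures says all enrolled patients are followed, and analysis sets are commonly left to a statistical analysis plan, which is not shown. The added steps are described as easy to master after training. A photograph shows visible non-conformity, and nothing in the article links failing the check to later reflux. The checkers are data managers, and nothing suggests that they know outcomes when they decide.

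Much of this stands. A reader might infer that the rule demonstrably strips technical failures from the uncut arm and so favours it. The documents do not show that: they give no rejection rate for either arm and no risk for rejected cases. A reader might also take the 13% figure as the expected error rate. It depends on assumed risks of 30% to 50% among rejected cases and on no control rejections at all; allowing half as many control rejections brings 12.7% down to 6.4%.

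The core is untouched. This is a stated rule, not a detail left out. Exclusion is the natural meaning of rejecting a case, and an analysis plan that kept everyone would contradict the article's wording. The Discussion's promise is only to count cases where the assigned treatment could not be performed. That is a different group from operations performed below standard, and a count does not keep anyone in the analysis.

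**Conclusion.** The point holds in this form: the article prescribes an exclusion after randomisation and after reveal that depends on how the assigned treatment was performed, and nothing in it retains these patients in an as-randomised analysis. Confidence is high that the rule exists and that it can bias the comparison. That the bias favours uncut Roux-en-Y is plausible from the extra steps and the new technique, but it remains an inference.

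The size cannot be derived. Under the assumptions shown, the artefact ranges from none to 2 points, and false superiority from the nominal 2.5% to about 13%. Without control rejections, the milder case of 5% rejected at 30% risk gives about 1 point and about 6%. It is worth correcting whatever the true rates are, because the loss of protection comes from the rule itself and the correction is cheap.

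**What to change.** Replace the rejection sentence under Uniformity in surgical performance with a statement that every randomised patient whose arm was revealed stays in follow-up and is analysed in the assigned arm for the primary analysis, whatever the photo check finds. Use the check for quality control and surgeon feedback, and to define a per-protocol sensitivity analysis. Report the number of failures, and the reasons, by arm.

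The change is one of wording in the analysis set and alters no operation or visit. Any case already rejected should be restored to follow-up as far as possible; the article does not say how many there are. The downside is that the as-randomised estimate may be slightly smaller than the per-protocol one.

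Judging D2 adequacy before reveal might look like a natural addition, but it is not a wording change. The described check is photo upload followed by data-manager review, so it would need an assessment during the operation. Recruitment was also due to finish by December 2018, so such a step might reach few patients. The fix does not depend on it.
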